# UROPOT: study protocol for a randomized, double-blind phase I/II trial for metabolism-based potentiation of antimicrobial prophylaxis in the urological tract

**DOI:** 10.1186/s13063-024-08526-7

**Published:** 2024-10-15

**Keywords:** Antimicrobial prophylaxis, Endourological procedures, Postoperative infections, Biofilm, Potentiated aminoglycosides

## Abstract

**Background:**

Urinary tract catheters, including Double-J or ureteral stents, are prone to bacterial colonization forming biofilms and leading to asymptomatic bacteriuria. In the context of asymptomatic bacteriuria, endourological procedures causing mucosa-inducing lesions can lead to severe infections. Antibiotic prophylaxis is warranted, yet its efficacy is limited by biofilm formation on stents. Biofilms promote antibiotic tolerance, the capacity of genetically susceptible bacteria to survive a normally lethal dose of antimicrobial therapy. The UROPOT study evaluates the effectiveness of a first-in-type metabolism-based aminoglycoside potentiation for (i) preventing infectious complications of asymptomatic bacteriuria during mucosa lesion-inducing endourological procedures and (ii) assessing its anti-tolerance efficacy.

**Methods:**

The UROPOT trial is a phase I/II single-center (Lausanne University Hospital (CHUV), Switzerland) randomized double-blinded trial. Over 2 years, patients with asymptomatic *Escherichia coli* and/or *Klebsiella pneumoniae* bacteriuria, undergoing endourological procedures, will be randomly allocated to one of three treatment arms (1:1:1 randomization ratio, 30 patients per group) to evaluate the efficacy of mannitol-potentiated low-dose amikacin compared to established standard treatments (ceftriaxone or amikacin standard dose). Patients will be recruited at the CHUV Urology Outpatient Clinic. The primary outcome is the comparative incidence of postoperative urinary tract infections (assessed at 48 h) between the investigational amikacin/mannitol therapy and standard (ceftriaxone or amikacin) antibiotic prophylaxis, defined by specific systemic symptoms and/or positive blood and/or urine culture. Secondary outcomes include assessing microbiological eradication through anti-biofilm activity, sustained microbiological eradication, and mannitol and antibiotics pharmacokinetics in blood and urine. Safety outcomes will evaluate the incidence of adverse events following amikacin/mannitol therapy and postoperative surgical complications at postoperative day 14.

**Discussion:**

UROPOT tests a novel antimicrobial strategy based on “metabolic potentiation” for prophylaxis enabling aminoglycoside dose reduction and targeting biofilm activity. The anti-biofilm effect may prove beneficial, particularly in patients who have a permanent stent in situ needing recurrent endourological manipulations strategies in preventing infections and achieving sustained microbiological eradication in pre-stented patients.

**Trial registration:**

The protocol is approved by the local ethics committee (CER-VD, 2023–01369, protocole 2.0) and the Swiss Agency for Therapeutic Products (Swissmedic, 701,676) and is registered on the NIH’s ClinicalTrials.gov (trial registration number: NCT05761405). Registered on March 07, 2023.

**Supplementary Information:**

The online version contains supplementary material available at 10.1186/s13063-024-08526-7.

## Introduction

### Background and rationale

Over the past two decades, minimally invasive endourological techniques have become the primary approach for managing urinary stones and obstructive pathologies, often requiring stent placement for extended periods. However, these stents are prone to colonization by urogenital flora, leading to biofilm formation and asymptomatic bacteriuria, with *Escherichia coli* and *Klebsiella pneumoniae* representing over 75% of pathogens [1]. Although asymptomatic bacteriuria itself is not harmful per se, it can escalate to severe infections like urosepsis during mucosal lesion-inducing endourological procedures (e.g., stone fragmentation and/or extraction, stent manipulations) [2, 3]. During endourological interventions, bacteria from ureteral stents or in suspension may spread systemically due to increased intraluminal pressure, potentially leading to symptomatic urinary tract infections (UTI) [4]. In patients with long-lasting or permanent stents, such as cancer patients with upper urinary tract obstruction, over 30% experienced at least one episode of urosepsis during stent exchanges [5–8]. Management of these infectious complications is challenging, exacerbated by the rise of extended spectrum beta-lactamase (ESBL) and multi-drug resistant bacterial strains, complicating antibiotic treatment and prophylaxis [9].

Due to the high risk of infectious complications, the Infectious Disease Society of America (IDSA) recommends a urine culture prior to manipulation to guide antibiotic prophylaxis, with third-generation cephalosporins or carbapenems being frequently used [7, 10]. However, use of beta-lactams is fraught with the development of resistance, necessitating novel strategies to alleviate pressure on first-line agents and decrease the use of broad-spectrum carbapenems [11]. This has prompted the use of aminoglycosides as standard antibiotic therapy for UTIs in Australia (*sahealth.sa.gov.au*). However, none of these regimens is effective against biofilms formed on foreign bodies such as stents [10, 12].

Biofilm-associated bacteria exhibit “antibiotic tolerance,” and thus survive otherwise lethal doses of antibiotics, highlighting the need for effective strategies. While quinolones have an anti-biofilm activity, resistance in Enterobacteriaceae like *E. coli* or *K. pneumoniae* approaches 20% in Switzerland (*anresis.ch*), limiting their utility in urinary tract infection management. Addressing the lack of biofilm eradication strategies, rising antibiotic resistance, and the steady increase in endourological interventions following previous ureteral stenting, the UROPOT study aims to evaluate the clinical significance of a novel antimicrobial strategy during mucosal lesion-inducing procedures in pre-stented patients with asymptomatic bacteriuria.

Previous research in a murine catheter-associated urinary tract infection (CAUTI) model has demonstrated that metabolic stimulation by substrates such as mannitol can enhance the efficacy of aminoglycosides in killing *E. coli*, including tolerant forms like biofilms [13, 14]. Moreover, the potentiation allows a reduction of aminoglycoside dosing [15]. Amikacin and mannitol are both approved for clinical use but exhibit differing safety profiles. Aminoglycosides such as amikacin can cause dose-dependent ototoxicity and nephrotoxicity [16]. In contrast, mannitol is used without major side effects and is not metabolized by host cells, being fully excreted by the kidneys. Pharmacological data suggest that low systemic doses of aminoglycosides achieve urine concentrations far exceeding the Clinical and Laboratory Standards Institute breakpoint for Enterobacteriaceae, and a single dose can sustain therapeutic levels against pathogens like *E. coli* for up to 3 days, making it a promising outpatient option [17, 18].

Based on the existing evidence, we designed a single-center randomized double-blinded pilot study (UROPOT: UROlogical infections and antibiotic POTentiation) with the aim of evaluating the clinical efficacy of metabolic potentiation in urinary tract antimicrobial therapy. Specifically, we will assess the combination of mannitol and low-dose amikacin for prophylaxis during endourological procedures in asymptomatic bacteriuria patients, comparing its prophylaxis efficacy to the current gold standard antibiotic prophylaxis regimen (ceftriaxone or amikacin standard dose alone). We will also assess its anti-biofilm activity compared to the gold standard regimens. UROPOT (ClinicalTrials.gov NCT05761405) is partially funded by the Leenaards Foundation’s Scientific prize and the University of Lausanne.

### Objectives

UROPOT is a single-center randomized double-blinded pilot study. Patients will be allocated randomly to one of three treatment arms (with a 1:1:1 randomization ratio) to evaluate the efficacy of mannitol-potentiated reduced-dose amikacin in comparison to established gold standard treatments (ceftriaxone or amikacin standard dose alone; Fig. 1). The primary outcome of the study is to compare the incidence of postoperative infections assessed at 48 h postoperatively, defined by specific systemic symptoms and/or positive urine/blood culture. Secondary outcomes include assessing microbiological eradication through anti-biofilm activity, sustained microbiological eradication (urine cultures at 48 h and 14 days), and pharmacokinetics of mannitol and antibiotics in blood and urine samples. We will further evaluate the incidence of adverse events following amikacin/mannitol therapy and postoperative complications according to the Clavien-Dindo classification at postoperative day 14 (safety outcomes) [19].

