### Participants/eligibility criteria

Patients with asymptomatic *E. coli* and/or *K. pneumoniae* bacteriuria, undergoing endourological procedures. Inclusion and exclusion criteria determining the eligibility of study participants are reported in Table 1. Bacteriuria is defined as ≥ 10^2^ CFU/ml for both *E. coli* and *K. pneumoniae*. In case of mixed cultures, *E. coli* and/or *K. pneumoniae* should be significantly more enriched than other bacteria (i.e., ratios of quantitative results in CFU/ml of *E. coli*/other bacteria or *K. pneumoniae*/other bacteria are > 100).

**Table 1 Tab1:** Inclusion and exclusion criteria of the UROPOT trial

Participants fulfilling all the following inclusion criteria are eligible for the study:
1. Written informed consent
2. Adults (≥18 years)
3. Patients with a ureteral stent in situ
4. Patients scheduled for endourological ureteral manipulations (e.g. endourological stone surgery, ureteral stent exchange)
5. Asymptomatic bacteriuria with strains of E. coli and/or K. pneumoniae sensitive to ceftriaxone and amikacin.
The presence of any one of the following exclusion criteria will lead to exclusion of the participant:
1. Allergy to one of the study drugs or excipients (Beta-lactams, aminoglycosides or mannitol)
2. Pregnant and lactating women
3. Glomerular filtration rate (CKD-EPI eGFR) < 50ml/min / 1,73m2
4. Middle to severe hearing impairment
5. Myasthenia gravis or other forms of myoneural disorders
6. Congestive heart failure, pulmonary oedema
7. Intracranial haemorrhage, compromised blood-brain barrier
8. Antibiotic treatment within 14 days prior to randomization
9. Mixed cultures of E. coli and/or K. pneumonia with other bacteria
10. Previous (within 3 months prior to randomization) or concomitant participation in another interventional clinical trial
11. Inability to understand and follow the protocol
12. Inability to give informed consent

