**Assessments:**						
Patient history, physical exam, pregnancy test		x				
Ureteral stent discomfort questionnaire		x			x	x
Vital signs (temperature, blood pressure, heart rate, and respiratory rate)		x		x	x	x
Blood draw for analyses: sodium, potassium, creatinine, eGFR (CKD-EPI), complete blood count		x^a^		x^b^	x	x^c^
Urine sampling for analyses: urine culture (microbiology)		x^a^		x^b^	x	x
**Assessment of anti-biofilm activity (secondary outcome)**				x		
Blood draw for analyses: aminoglycoside + mannitol level (AMK/Man level) at 1, 3, and 6 h after administration of drug				x		
Urine sampling for analyses: ceftriaxone, mannitol, and aminoglycoside levels in urine				x (during intervention)	x	
**Assessment of post-interventional clinical UTIs (primary outcome)**					x	X

^a^By phone

^b^Blood draw at 1/3/6 h post-infusion; urine culture intraoperatively

^c^Only if abnormal values at V2

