### Study endpoints

The primary outcome is the rate of postoperative infections 48 h postoperatively. Postoperative infections include systemic symptoms and positive urine/blood cultures matching preoperative urine cultures as deemed by the adjudication committee. Secondary outcomes include microbiological eradication via anti-biofilm activity assessed through catheter sonication, quantitative culture, and intraoperative urine culture; sustained microbiological eradication measured by urine cultures at postoperative days 2 and 14; and primary pharmacokinetic parameters of mannitol and antibiotics in blood and urine samples at specified time points. Safety outcomes will include monitoring the incidence of adverse events related to amikacin/mannitol combination therapy throughout the study, including serious adverse events (SAEs) and pre-specified adverse events of special interest such as ototoxicity and nephrotoxicity, along with vital signs. Additionally, postoperative complications at day 14 will be assessed using the Clavien-Dindo classification [19].

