### Statistical analysis

The primary outcome is the proportion of postoperative infections within 48 h postoperatively. Fisher’s exact test will applied to compare the proportions between mannitol + low-dose amikacin arm vs full-dose amikacin arm and mannitol + low-dose amikacin arm vs ceftriaxone arm, respectively. To account for multiple comparisons, single-step method will be applied to control the family-wise error rate. Odds ratios with 95% confidence intervals and associated *p* value will be reported. Due to its exploratory nature and limited number of participants, no interim analysis will be performed. Microbiological eradication will be compared between the same groups mentioned in the primary analysis using *t*-tests. Difference in means with 95% confidence intervals and *p* values will be reported. If normality assumption is not met and the data approximately follow a log-normal distribution, data will be log-transformed before applying *t*-tests. In this case ratios of geometric means with 95% confidence intervals and *p* value will be reported. If none of the above methods hold, non-parametric methods will be considered.

Sustained microbiological eradication will be analyzed using mixed-effects models to account for the repeated measurements. Fixed effects will be the baseline microbiological eradication measured at D0, the intervention, the visit (D2 and D14), and the interaction between the intervention and the visit. Subject-specific random effect will be considered. Statistical assumptions will be assessed, and a similar methodology will be applied as for microbiological eradication to addressed them.

Primary pharmacokinetic parameters in blood (Cmax, AUC, t1/2) will be calculated for mannitol, amikacin, ceftriaxone, and for each intervention arm. In urine, descriptive statistics will be reported without any specific comparisons and spot urine concentrations.

Planned analyses will adhere to the sections detailing primary, secondary, and safety analyses, with a statistical analysis plan finalized and signed by all parties before code break. Datasets for analysis include the intention-to-treat (ITT), per-protocol (PP), and safety populations, with primary and secondary outcomes assessed in the ITT population and safety outcomes analyzed in the safety population.

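### The primary outcome has two conflicting case definitions, and the broader one, read literally, counts symptom-free persistent bacteriuria as a postoperative infection

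*Protocol article*

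**What the plan says.** The protocol article describes the primary event in five places.

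- **Abstract, Methods:** "defined by specific systemic symptoms and/or positive blood and/or urine culture".
- **Objectives:** "defined by specific systemic symptoms and/or positive urine/blood culture".
- **Study endpoints:** "Postoperative infections include systemic symptoms and positive urine/blood cultures matching preoperative urine cultures as deemed by the adjudication committee".
- **Table 2, Assessments:** the row is labelled "Assessment of post-interventional clinical UTIs (primary outcome".
- **Statistical analysis:** "The primary outcome is the proportion of postoperative infections within 48 h postoperatively". The case definition is not repeated there.

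Three other statements bear on how these read. Inclusion criterion 5 in Table 1 is "Asymptomatic bacteriuria with strains of E. coli and/or K. pneumoniae sensitive to ceftriaxone and amikacin". The accompanying text sets a low entry threshold: "Bacteriuria is defined as ≥ 10^2^ CFU/ml for both" species. The Background describes the entry state this way: "Although asymptomatic bacteriuria itself is not harmful per se". Table 2 schedules a repeat urine culture at Visit 2 (day 2), and that culture also feeds the secondary outcome of sustained microbiological eradication.

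**The concern.** The descriptions differ in two respects. The abstract and Objectives join symptoms and culture by *and/or* and ask for no match to the baseline organism. Study endpoints joins them by *and* and asks for a match.

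In patients with sterile urine at entry this might be loose drafting of little consequence, because a new positive culture would at least be a new event. Here every patient is culture-positive and symptom-free by design. Under the literal *and/or* rule, a patient who leaves theatre well and whose entry strain is still present at 48 h counts as a postoperative infection. The patient's condition has not changed, and the article itself regards that condition as benign.

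What is at stake is the question that the primary comparison answers. One rule measures failure to prevent clinical infection. The other mixes that with failure to clear the urine, which the trial already measures as a secondary outcome. The primary outcome is tested with Fisher's exact test in two comparisons under family-wise error control, and that control has a clear meaning only if the event is fixed before the code is broken.

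**Working it through.** **No figure in the plan to reproduce.** The sample size of 30 per group rests on practical considerations (Sample size section), and 3 × 30 = 90 agrees with Trial design. No event rate, power or numerical alpha is stated, so no number in the plan depends on the definition.

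**Step 1: classify each type of patient under each rule.** Culture here means a urine or blood culture at 48 h.

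| Patient at 48 h | Abstract and Objectives (*and/or*) | Study endpoints (*and*, matching) |
|---|---|---|
| Symptoms, matching culture | event | event |
| Symptoms, non-matching culture | event | not an event |
| Symptoms, culture negative | event | not an event |
| No symptoms, entry strain still in urine | event | not an event |
| No symptoms, culture negative | not an event | not an event |

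The rules disagree in three of the five rows. The fourth row matters most, because all participants start there.

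**Step 2: test the loose reading of Study endpoints.** That sentence says infections *include* the two elements, so it could be a list of components and not a joint requirement. The connectives would then agree, but the fourth row would become an event under both descriptions, and the matching clause would still appear in only one of them. The loose reading does not remove the problem.

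**Step 3: illustrate the size.** All rates here are assumptions. Let s be the proportion with systemic symptoms (5–30%) and b the proportion with a positive urine culture at 48 h (20–60%). Organism matching and blood cultures are ignored.

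If the two groups overlap as far as possible, which makes the gap smallest:

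- *and*: 30 × min(s, b)
- *and/or*: 30 × max(s, b)

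| s | b | *and*, per 30 | *and/or*, per 30 |
|---|---|---|---|
| 5% | 20% | 1.5 | 6 |
| 5% | 60% | 1.5 | 18 |
| 10% | 40% | 3 | 12 |
| 20% | 20% | 6 | 6 |
| 30% | 20% | 6 | 9 |
| 30% | 40% | 9 | 12 |
| 30% | 60% | 9 | 18 |

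The ranges are 1.5–9 and 6–18. The rules coincide only where the symptomatic and the culture-positive patients are the same people (the 20%/20% row). In the 30%/20% row the three extra events are symptomatic patients without a positive culture, so the disagreement is not always about bacteriuria.

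If symptoms and culture were independent, *and* is 30sb and *and/or* is 30(s + b − sb). Over the same ranges this gives 0.3–5.4 against 7.2–21.6.

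**Step 4: consequence for the test.** Take the same relative effect, a halving of risk, at different base rates. Exact Fisher power with 30 per arm and an assumed two-sided 0.05 is about 2% for 10% vs 5%, 30% for 40% vs 20%, and 56% for 60% vs 30%. At 0.025, a Bonferroni stand-in for the single-step adjustment, the figures are about 2%, 20% and 45%.

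**The case against.** The strongest reply is that the article, read as a whole, already points one way. The endpoints section is the proper home of the definition and the only place where the adjudication committee appears. Table 2 speaks of clinical UTIs, and the Background separates harmless bacteriuria from infection. The abstract and Objectives are summaries. This largely stands: a symptom-free carrier is unlikely to be the intended case. A reader might infer that the committee could apply either rule and be equally faithful to the document, but the text does not support that. It remains true that two current statements of the primary outcome say otherwise and that the Statistical analysis section does not choose.

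A second reply is that the full protocol or an analysis plan may settle the matter. It may. The point here is not missing detail, though. The article contradicts itself on its primary endpoint.

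A third reply is that the 48 h positivity rate may be low. Entry strains must be susceptible to both ceftriaxone and amikacin, and the Background says one aminoglycoside dose can hold therapeutic levels against *E. coli* for up to 3 days. On the symptom side, the Background's figure of over 30% with urosepsis is the share of long-term stent patients with at least one episode, so it is not a rate per procedure. This stands in full: the documents do not allow the gap to be sized.

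**Conclusion.** The inconsistency is real and concerns the primary endpoint. Taken literally, the *and/or* wording is a wrong rule for this population, because it turns unchanged baseline status into an event. The table of patient types shows this without any assumed rate.

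The size is illustrative only. On the assumed ranges with maximal overlap, the counts are 1.5–9 against 6–18 per 30 patients, and the gap can be small (9 against 12, 6 against 9) or nil (6 against 6).

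Three stronger conclusions might be inferred and are not supported:

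- **A single fold-difference.** With maximal overlap the ratio runs from 1 (6 against 6) to 12 (1.5 against 18). Under independence it runs from 4 (0.72/0.18) to 24 (0.24/0.01). It reflects the assumptions, not the trial.
- **A reversed comparison between arms.** This is conceivable, but nothing in the documents or the arithmetic shows it.
- **Redundancy with the eradication outcome.** The overlap is partial. Sustained eradication is modelled over days 2 and 14 with a day 0 covariate by mixed-effects models, whereas the primary is a binary 48 h event that also takes in symptoms and blood cultures.

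The exploratory aim and the practical basis for the sample size do not remove the need to settle the rule before code break, since a choice made afterwards could be influenced by the results.

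**What to change.** Before code break:

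1. Reconcile the abstract, Objectives, Study endpoints and Statistical analysis to one case definition, in line with the endpoints section and Table 2.
2. State that a positive urine culture without symptoms is not a primary event and is counted only under microbiological eradication.
3. Have the investigators state how two remaining groups are classified: symptomatic patients with a negative culture, and patients with a positive blood culture but no recorded symptoms. A strict *and* would exclude both, and that choice is theirs.
4. Apply the single definition to all adjudicated cases, including any already decided, while still blinded.

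The cost is wording, plus a modification submitted to the ethics committee and Swissmedic, as the Trial status section requires for any protocol change. The sample size and the visit schedule are unaffected, and the cultures and clinical assessments needed are already planned. Whether any case has yet been adjudicated cannot be seen from the article. If some have, re-reading them is the only added work.
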